### Recruitment {15}

Participants meeting the inclusion criteria will be approached by their treating paediatrician.

### Assignment of interventions: allocation

#### Sequence generation {16a}

A randomisation sequence will be generated in advance using a computer algorithm. Each value in the sequence corresponds to a number of days between ten and eighteen, determining the timing of the intervention period (T1) relative to the start of the daily progress monitor (T0).

#### Concealment mechanism {16b}

The pre-generated randomisation sequence will be stored in a fixed list. Participants will be assigned start dates based on the order of recruitment, following the sequence exactly. This procedure ensures consistent application of random allocation while avoiding selection bias.

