#### Who will take informed consent? {26a}

Potential participants will receive oral and written information from the executive investigator.

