#### Implementation {16c}

Investigators enrolling participants will assign each individual the next start date in the sequence. If a participant’s assigned start date falls on a weekend, the intervention will begin on the nearest weekday (the preceding Friday or following Monday).

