### Assignment of interventions: blinding

#### Who will be blinded {17a}

The analysis of the ESM data will be performed by an independent statistician with no involvement in participant recruitment or access to identifying information. Both the statistician and the investigator will refer to participants solely by their study codes (e.g. B02) to ensure confidentiality and minimise bias.

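### The plan describes no step that hides the next start interval from the investigators who enrol, so its statement that the procedure avoids selection bias is unsupported

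*Protocol article*

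**What the plan says.** Under Sequence generation {16a}, the Protocol article states: "A randomisation sequence will be generated in advance using a computer algorithm". Each value is a number of days from ten to eighteen between T0 and T1.

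The section headed Concealment mechanism {16b} has three sentences. The first concerns storage: "The pre-generated randomisation sequence will be stored in a fixed list". The second gives the rule of use: "Participants will be assigned start dates based on the order of recruitment, following the sequence exactly". The third draws the conclusion: "This procedure ensures consistent application of random allocation while avoiding selection bias".

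Implementation {16c} names who applies the list: "Investigators enrolling participants will assign each individual the next start date in the sequence". It adds a calendar adjustment: "If a participant’s assigned start date falls on a weekend, the intervention will begin on the nearest weekday".

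On roles, the consent section {26a} says: "Potential participants will receive oral and written information from the executive investigator". The same executive investigator delivers the intervention (Booster intervention). The study team checks the remaining exclusion criteria (Eligibility criteria {10}), and the treating paediatrician makes the first approach (Recruitment {15}). The only separation of roles described is for analysis of the ESM data, by "an independent statistician with no involvement in participant recruitment" (Who will be blinded {17a}).

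The statistical methods for RQ1 make randomisation of the start a precondition of the single-case randomisation test (SCRT) and credit it with controlling time-related confounding.

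**The concern.** Generating a list in advance and using it strictly in order is normal practice and not a fault. It ensures that nobody skips or reorders entries. Concealment is a different property: whoever decides on enrolment and timing must not know the next entry when deciding. The section meant to describe that property names no holder of the list, no limit on access, and no rule that enrolment and T0 are fixed before the interval is released. The following section has the enrolling investigators draw the entry themselves. The conclusion about selection bias therefore does not follow from the procedure given.

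What is at stake is specific to this design. There is no control arm to steer patients away from. The SCRT compares the observed level change with the changes at the other possible start points, and it is valid because the start is random relative to whatever else happens in the participant's life. The list randomises an interval, not a date. If the interval is known first and T0 is set afterwards, the dates of T1, and of T2 about four weeks later, are open to choice. In adolescents, school holidays or test weeks could plausibly shift fatigue, self-efficacy and attendance.

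**Working it through.** **1. Does the text give a concealment step?** Concealment needs three things: a holder separate from enrolment, a release point after enrolment, and T0 fixed before release. Set against sections {16a} to {17a}, holder: not stated; release point: not stated; order of T0 and release: not stated. The one independent person named has a task in ESM analysis only. The article also does not say that investigators can see later entries. The textual finding is therefore that concealment is claimed but not shown.

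**2. Inputs for an illustration.** From Sample size {14} and Table 1: 20 cases, start range 18 − 10 + 1 = 9, 130 daily measurements, autocorrelation 0.30, 30% missing. Phase B for fatigue-related self-efficacy (FSE) starts at T2, four weeks after T1, so the phase change falls between day 10 + 28 = 38 and day 18 + 28 = 46. Assumed, not in the article: alpha 0.05 one-sided, data missing at random, stationary AR(1) errors with unit variance, test statistic = mean over cases of (phase B mean − phase A mean), and p-value from random re-draws of the nine starts.

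**3. The plan's own figure.** With an effect of 0.7, simulated power is 0.82 with the phase change at T2 (1,000 trials), in line with the stated ≥ 0.80. With no effect and random starts, the rejection rate is 0.057, against a nominal 0.05 with Monte Carlo standard error √(0.05 × 0.95 / 1,000) = 0.007.

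**4. No intervention effect, but an outside event.** Suppose an event raises the outcome by 0.5–0.7 SD in a share of cases. Each range below pools several independent simulation runs and both shift sizes.

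| How the event relates to T2 | 25% of cases | 50% of cases |
|---|---|---|
| T0 set without knowing the interval | about 0.04–0.06 | about 0.04–0.06 |
| T0 timed so that T2 meets the event exactly | 0.10–0.17 | 0.23–0.39 |
| Timed, with error uniform within ±3 days | 0.08–0.10 | 0.11–0.17 |
| Timed, with error uniform within ±5 days | 0.07–0.08 | 0.10–0.12 |

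The first row shows that an outside event by itself does no harm: the test holds its level when the interval is unknown at T0. The inflation needs both foreknowledge and its use, and it falls quickly once alignment is imprecise, because the start range is only nine days wide. The shift and the shares are assumptions; nothing in the article indicates what they might be.

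**The case against.** The strongest reply is that silence is not an open list. Assigning the next entry in order of recruitment is compatible with an interval revealed only after enrolment, and a journal article may leave custody of the list to the full protocol. This stands in part. A reader might infer that the allocation was in fact visible, or that the SCRT is invalid; the article supports neither. What it does contain is a positive statement about selection bias, and the procedure given as its reason does not deliver it. That is an unsupported claim rather than an omitted detail.

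A reader might also infer that investigators could choose whom to enrol for a favourable interval. This route is weak. All participants receive Booster and serve as their own control, entries differ by at most 18 − 10 = 8 days, and the paediatrician makes the first approach. It is hard to see how such a choice would bias a within-person contrast.

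The timing route also has limits. The investigator would have to foresee an event 38 to 46 days after T0. T2 can drift, because the Measurement Period may be extended when compliance is below 70%, because weekend starts are moved, and because T1 and T2 are face-to-face appointments. The tested change for the other outcomes comes four or six weeks after T2, so one choice of T0 would not align them all. These points make exact-day alignment a worst case and the ±3-day or ±5-day rows more realistic. They do not supply the missing safeguard.

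**Conclusion.** The point holds in a limited form. As described, the procedure gives consistent application of a random sequence but no concealment of the next interval, so the statement about selection bias should not stand on it. The relevant exposure is the choice of T0 with the interval already known, which would let the dates of T1 and T2 be chosen and so weaken the basis of the group-level causal test.

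The article does not show that this occurred, and its size cannot be derived from it. Under the assumed shifts of 0.5–0.7 SD, type I error would be roughly 0.08–0.10 (25% of cases timed) to 0.11–0.17 (50%) with a ±3-day error; the larger figures of 0.10–0.17 and 0.23–0.39 require alignment to the day. If T0 was always fixed first, the error stays near 0.05. The stated sample size, start range and power are unaffected.

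**What to change.** For any participant still to be enrolled, have the list held by someone outside enrolment (the independent statistician already named would do) or by the app's back-end. Release each interval only after consent, eligibility and the T0 date have been logged.

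Recruitment began in October 2024 and was expected to end in April 2025, and this protocol version is dated March 2025. For most participants, then, the remedy is reporting: state who could see the list, and whether T0 was fixed before the interval was known. Unless such a safeguard was in place, withdraw the statement that the procedure avoids selection bias and keep only the statement about consistent application.

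The cost is one or two procedural sentences and one message per participant still to be enrolled.

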#### Implementation {16c}

Investigators enrolling participants will assign each individual the next start date in the sequence. If a participant’s assigned start date falls on a weekend, the intervention will begin on the nearest weekday (the preceding Friday or following Monday).

### Assignment of interventions: blinding

#### Who will be blinded {17a}

The analysis of the ESM data will be performed by an independent statistician with no involvement in participant recruitment or access to identifying information. Both the statistician and the investigator will refer to participants solely by their study codes (e.g. B02) to ensure confidentiality and minimise bias.

#### Procedure for unblinding if needed {17b}

Not applicable.

### Data collection and management

#### Plans for assessment and collection of outcomes {18a}

Study outcomes will be assessed using the daily progress monitor, a repeated survey. The Booster app sends the daily progress monitor at a random time within the hour before bedtime. Participants determine the exact timing of completing the monitor, provided it is within three hours of receiving the notification. Responses not submitted within this three-hour window are considered missing. For each item, participants are asked to reflect on their day. Item order is randomised to minimise method bias [56]. The daily monitoring period starts ten to eighteen days before the Start Conversation and continues for 130 days, ending twelve weeks into the Experiment Period.

#### Fatigue-related self-efficacy

To make the daily progress monitor feasible, a single item for FSE was constructed to measure one’s confidence in dealing with fatigue. Face validity was confirmed after three rounds of interviews with adolescents with (a history of) severe fatigue. The items tested in each round were based on items from validated self-efficacy questionnaires (Suppl. File 1). The resulting item (translated from Dutch) is “Today I believed that I could prevent fatigue from bothering me”. FSE will be scored on a VAS scale from 0 (“I didn’t believe it at all”) to 100 (“I believed it completely”), with higher scores indicating higher FSE. Likert options are shown on the answering scale (e.g. “I believed it a bit” for scores 21 to 40) instead of the exact score selected (e.g. 26).

#### Other study outcomes

*Fatigue severity* will be measured with the four-item pSFQ, answered on a seven-point Likert scale from “Yes, that is correct” to “No, that is not correct” [45]. The pSFQ score ranges from 4 to 28, with higher scores reflecting more severe fatigue. It has good psychometric properties, including Cronbach alpha’s ranging from 0.84 to 0.94 [45]. In the official pSFQ, respondents are instructed to think of the past two weeks. For the daily progress monitor in this study, the instruction was adapted to think of today.

*Participation* will be measured as school or work presence, which is calculated by the hours present divided by the hours scheduled multiplied by 100. For each working or school day, participants will fill in the number of hours on their personal timetable and the number of hours attended. This item is adapted from the PROactive cohort study [57].

*Life satisfaction* will be measured with the Cantril Ladder, adapted for adolescents [58]. Respondents rate their life with a ladder numbered from zero to ten. The bottom represents “The worst possible life”, and the top ‘The best possible life”. This version of the Cantril Ladder is extensively used in the Netherlands. It has good reliability and convergent validity with other well-being measures [58].

*Perceived health* will be measured with the EuroQol (EQ) visual analogue scale (VAS) [59]. Respondents rate their current health on a vertical scale from 0 (“The worst health you can imagine”) to 100 (“The best health you can imagine”). The scale shows the exact number selected. Rating their health status is feasible for adolescents, and EQ-VAS scores can predict health-related QoL as measured by the EQ Five Dimensions Health Questionnaire (EQ-5D) [59].

#### Goal attainment

The daily progress monitor will also be used to evaluate goal attainment on a personalised frequency during the Experiment Period (see section “Stage 4: Experiment Period”). For example, if the goal is to cycle to school on Mondays, Thursdays, and Fridays, the goal evaluation will only take place on those days.

#### Demographics and potential covariates

To characterise participants, the following parameters will be obtained at baseline: age, sex, primary diagnosis and time since diagnosis, fatigue duration, and level of education. Additional questionnaires to be completed at baseline and follow-up are the multiple-item questionnaires measuring the same constructs as measured by the daily ESM progress monitor. Moreover, potential predictors, mediators, and moderators of the primary outcome FSE will be assessed. These potential covariates are internalising symptoms, pain, illness identity, mastery, and physical activity (Suppl. Table 6 for an overview of baseline and follow-up assessments).

##### Qualitative evaluation

A semi-structured interview will be conducted with each participant at the Evaluation Conversation by the investigator. The first aim is to gain understanding of Booster’s effect, and internal and external factors influencing this effect, as experienced by the participant. The second aim is to evaluate the Booster intervention in general and the Booster app specifically. Before the interview, participants will fill in a short Booster-tailored usability questionnaire (Suppl. File 2). The questionnaire will also ask about the effect of Booster (e.g., “What is the effect of Booster on you?”). In the second part of the interview, follow-up questions will be asked about motivation, feasibility, and usability (Suppl. File 3). This will guide potential future development steps. Interviews will be audio recorded and transcribed verbatim. The interview and the usability questionnaire combined will support the interpretation of the quantitative single-case outcomes.

#### Plans to promote participant retention and complete follow-up {18b}

To reduce the burden of repeatedly filling out the daily progress monitor, we aimed to include as few items as possible for each construct while maintaining good psychometric properties. To increase compliance, game mechanics were added (see section “Stage 2: Measurement Period”) and the daily assessment time is personalised based on participants’ bedtimes.

#### Data management {19}

A data management plan has been written and reviewed by UMC Utrecht’s data quality management team.

#### Confidentiality {27}

All data will be handled in accordance with the General Data Protection Regulation (GDPR). Only members of the research team directly involved in the study will have access to participant codes and associated data. Electronic data will be stored on secure, password-protected systems that comply with UMC Utrecht’s information security standards. Physical documents, including signed informed consent forms, will be stored in a locked cabinet at the Wilhelmina Children’s Hospital. In the event of data sharing after the study has ended, all datasets will be anonymised to protect participant privacy prior to release.

#### Plans for collection, laboratory evaluation and storage of biological specimens for genetic or molecular analysis in this trial/future use {33}

Not applicable.

## Statistical methods

### Statistical methods for primary and secondary outcomes {20a}

#### RQ1: What is the effect of the Booster intervention on the study outcomes at the group level?

We will study change in mean level of outcomes (level change) after outcome-specific lags (Suppl. Figure 1). We hypothesise that FSE, Booster’s main target, will improve immediately after the Insight Conversation. Improvements in fatigue and participation are expected four weeks later, with life satisfaction and perceived health improving at six weeks post-Insight Conversation. After visual inspection of the data, the multiple baseline SCRT will determine the presence of significant medium to large Booster intervention effects at the group level. The null hypothesis is that observed outcomes are independent of intervention phase. The randomisation of intervention start is a precondition for conducting the SCRT. It tests significance by comparing the observed test statistic (mean level change) to the test statistic distribution of all other possible intervention start points. This controls for time-related confounding [60, 61]. The SCRT outcomes will show if the Booster intervention is effective at the group level.

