### Objectives {7}

The primary objective of the study is to examine the effect of the Booster intervention on FSE and the other study outcomes: fatigue severity, school participation, life satisfaction, and perceived health. Study outcomes will be evaluated at the group level (research question (RQ) 1) in adolescents (12 to 18 years) with a chronic health condition in a stable phase. Participants will have experienced hindrance by fatigue for at least 3 months. We hypothesise that FSE increases first, followed after four weeks by decreased fatigue severity, and after six weeks by improved school participation, life satisfaction, and perceived health.

The secondary objective is to gain insight into individual differences regarding (moment of) significant change in outcomes during the Booster intervention. At the single-case level, we will explore which participants show change in outcomes (RQ2) and when these responders start to show change (RQ3). In addition, at group level, we will study whether baseline participant characteristics are predictive of improvements during the Booster intervention (RQ4) and whether long-term change can be observed (RQ5).

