### Outcomes {12}

The primary outcome of the study is FSE. Other outcomes are fatigue severity, school participation, life satisfaction, and perceived health (see “Plans for assessment and collection of outcomes”).

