### Sample size {14}

The power to detect an intervention effect with a multiple baseline design (RQ1) depends on the autocorrelation of consecutive daily progress monitor measurements, the start moment range, the number of repeated measurements, the intervention effect, and the number of cases [52]. In the earlier PROfeel study [48], the median autocorrelation of weekly measurements was 0.17 for FSE, 0.30 for fatigue severity, and 0.09 for QoL. Median autocorrelation of the five times daily ESM item on fatigue severity was 0.37 [48]. We expect the daily measurements in this study to show a higher autocorrelation than weekly measurements, but lower than a five times daily item. Thus, we assumed the autocorrelation in our study to be 0.30 across outcomes. The start moment range is nine, as the Booster intervention is randomised to start (T1) ten to eighteen days after the start of the daily progress monitor (T0). With 100% compliance, the number of repeated measurements is 130. With the abovementioned assumptions and inclusion of twenty cases, with up to 30% of daily measurements missing, the multiple baseline single-case randomisation test (SCRT) can detect medium to large intervention effects of ≥ 0.7 with a power of ≥ 0.80 at the group level (RQ1, Table 1). However, we anticipate small intervention effects since Booster is an early intervention, not treatment. The SCRT, used in SCED, has limited power to detect such small intervention effects [37, 52, 53]. In contrast, the permutation distancing test (PTD), developed for testing differences in means in single-case observational designs (SCODs), exhibits higher statistical power [53]. It is important to note that SCOD cannot establish causality. With the abovementioned assumptions, with up to 40% of daily measurements missing, the study is well powered to observe changes in outcomes for effect sizes as small as 0.3 at the single-case observational level (RQ2, Table 1).

**Table 1 Tab1:** Power for detecting intervention effects at the group and single-case level

Factors influencing power	Study design	
Autocorrelation (%)	30	
Repeated measurements (*n*)	130	
Power (%)	≥ 80	
Cases (*n*)	20 (group level)	1 (single-case)
Test	Multiple baseline SCRT	PDT
Start moment range (*n*)	9	NA
Maximum percentage missing data to retain sufficient power (%)	30	40
Minimum detectable effect size	0.7 (medium to large)	0.3 (small)

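### FSE is named the one primary outcome, but the group-level effectiveness conclusion under RQ1 is not tied to it

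*Protocol article*

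**What the plan says.** Three places in the protocol article bear on this.

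- **Outcomes {12}** ranks the outcomes: "The primary outcome of the study is FSE", followed by "Other outcomes are fatigue severity, school participation, life satisfaction, and perceived health".
- **Objectives {7}** does not keep that ranking: "The primary objective of the study is to examine the effect of the Booster intervention on FSE and the other study outcomes". All five outcomes are assigned to RQ1. The secondary objective covers individual differences, timing of change, predictors and long-term change. It does not take in the group-level effect on the other four outcomes.
- **Statistical methods {20a}, RQ1** plans the tests: "We will study change in mean level of outcomes (level change) after outcome-specific lags". It adds that "the multiple baseline SCRT will determine the presence of significant medium to large Booster intervention effects at the group level", and closes with "The SCRT outcomes will show if the Booster intervention is effective at the group level".

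FSE is given priority elsewhere too. RQ1 calls it the main target of the intervention, RQ4 defines responders by FSE alone, and both the covariates section and the Discussion refer to it as the primary outcome. No section states an alpha level, sidedness, or a correlation between outcomes.

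**The concern.** RQ1 is the only analysis from which the protocol draws a causal conclusion. Sample size {14}, RQ2 and the Discussion all say that the single-case tests cannot establish causality, and the Discussion relies on the multiple baseline design to show effectiveness at the group level. What counts as success in RQ1 is therefore what the trial may claim.

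Outcomes {12} implies that FSE decides. The closing sentence of RQ1, read with Objectives {7}, allows a conclusion from the SCRT results on any of the five outcomes. The two readings part when FSE is not significant and another outcome, say perceived health, is. One reading then says effectiveness was not shown, and the other permits the claim. Such a result would also fit poorly with the protocol's own hypothesis, in which FSE changes first and the other outcomes follow.

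This situation is realistic. Sample size {14} and the Discussion both expect effects smaller than the SCRT can reliably detect, so a null FSE result is a plausible outcome of the trial.

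**Working it through.** **1. The plan's own figure.** Sample size {14} and Table 1 give power of at least 0.80 for an effect of 0.7, with 20 cases, 130 daily measurements, autocorrelation 0.30, nine possible start days and up to 30% missing. This was checked by simulating the multiple baseline SCRT: AR(1) errors with marginal SD 1, mean level change averaged over cases, 999 random start combinations, 1,000 simulated trials, and an assumed alpha of 0.05.

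- Change at the Insight Conversation, as RQ1 hypothesises for FSE (28 days after the randomised start): power 0.82.
- Change four or six weeks after that: 0.84 and 0.83.
- Change already at the Start Conversation: 0.71. RQ1 does not place the FSE effect there.

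The stated power is thus reproduced for a single SCRT timed as RQ1 describes. At a true effect of 0.5, power for FSE is 0.585, so FSE would be missed in 1 − 0.585 = 0.415 of trials. This supports treating a null FSE result as realistic.

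**2. Error rate if FSE alone decides.** One test at the assumed 5%: 5%.

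**3. Error rate if any of five tests sufficed.**

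- Inputs from the document: five outcomes (one primary, four other), each tested with its own lag.
- Assumed inputs: 5% per test, no adjustment, no true effect on any outcome, and a common correlation ρ between the five test statistics. The 0.30 in Sample size {14} is autocorrelation over time within an outcome and does not supply ρ, so a range is shown.

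If independent: 1 − (1 − 0.05)^5 = 1 − 0.95^5 = 0.226.

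If correlated, let Z_j = √ρ·G + √(1 − ρ)·E_j for j = 1 to 5, with G and E_j independent standard normal. The rate is P(max Z_j > 1.645) one-sided, or P(max |Z_j| > 1.96) two-sided. With 2,000,000 draws per cell:

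| ρ | one-sided | two-sided |
|---|---|---|
| 0 | 22.7% | 22.6% |
| 0.3 | 19.4% | 20.9% |
| 0.5 | 16.6% | 18.3% |
| 0.7 | 13.5% | 14.8% |
| 0.8 | 11.7% | 12.7% |
| 1 | 5.0% | 5.0% |

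Over ρ from 0.8 to 0 this is about 12% to 23%, or 11.7/5 = 2.3 to 22.6/5 = 4.5 times the nominal rate.

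**4. The part in dispute.** P(any of five significant) − P(FSE significant) is the probability that FSE is not significant but another outcome is. Under no effect this is 11.7 − 5 = 6.7 percentage points at ρ = 0.8 (one-sided), and 22.6 − 5 = 17.6 points at ρ = 0. These are the trials in which the two readings give different conclusions.

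**The case against.** The strongest reply is that the protocol already answers the question. It names one primary outcome, calls the rest other outcomes, and treats FSE as primary in several further sections. By ordinary convention the primary outcome decides, and the error rate is then nominal. The closing sentence of RQ1 follows a description of how the SCRT works, and may mean only that the test's results bear on effectiveness. On this view the point is one of phrasing.

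Much of this stands. A reader might infer that the plan has no hierarchy and lets any of five tests prove effectiveness. The documents do not support that: a ranking exists, and no any-of-five rule is written. A reader might also conclude that the plan has a particular inflated error rate. It does not, because every inflated figure above needs the unwritten rule, an assumed alpha and an assumed correlation. Nor is the absence of a multiplicity procedure a finding, since one may sit in an analysis plan that is not shown.

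What the reply does not remove is the mismatch on the page. Objectives {7} puts all five outcomes in the primary objective, and RQ1 draws its conclusion without naming FSE. An adjustment in an unseen analysis plan would not by itself settle which outcome the published conclusion rests on.

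**Conclusion.** The point holds as an inconsistency. FSE is ranked first under Outcomes {12}, but that ranking is not carried into the primary objective or into the only causal conclusion. A claim of effectiveness resting on another outcome is left open when FSE is null.

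Its size is conditional. At an assumed 5% per test, the false-claim rate is 5% if FSE alone decides, and about 12% to 23% if any unadjusted test of five sufficed, for assumed between-outcome correlations of 0.8 down to 0. Above 0.8 it falls further, reaching 5% at a correlation of 1. The range shows what the ambiguity could cost. It is not an error rate that the plan commits to. The correction is worth making before analysis because it settles what the trial may conclude and takes nothing from the FSE test.

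**What to change.** - **Statistical methods {20a}, RQ1:** replace the closing sentence with one to this effect: *The SCRT on FSE alone decides whether Booster is effective at the group level. The SCRTs on the other four outcomes are secondary and supportive, and cannot carry that claim if the FSE result is not significant.* A Holm correction among the four after a significant FSE result is optional.
- **Objectives {7}:** limit the primary objective to the effect on FSE, and list the group-level effects on fatigue severity, school participation, life satisfaction and perceived health as secondary.

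The cost is wording only. Design, data collection and sample size stay as they are, and the FSE test keeps its full alpha and its power (0.82 in the check above). The downside is small but real: if FSE misses significance, a significant result on another outcome can be reported as supportive but cannot establish effectiveness.
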